#### 12.2. Observation and Inspection Items

- (1) Basic information of research subjects: age, gender, history of treatment of diseases
- (2) MDS-UPDRS
- (3) Cognitive function assessment: MMSE, FAB, MoCA-J
- (4) QOL evaluation: PDQ-39
- (5) Evaluation of gait questionnaire (FOG-Q)
- (6) Evaluation of walking ability: walking distance in 30 seconds, 10m natural walking time and number of steps, Timed Up and Go test
- (7) Video recording of walking conditions

#### 12.3. Observation and Inspection Methods

- (1) Basic information of study subjects: age, gender, PD treatment history → excerpts from medical records
- (2) Examination by a neurologist → MDS-UPDRS
- (3) Evaluation of cognitive function: MMSE, FAB, MoCA-J → evaluation by a neurologist
- (4) QOL evaluation: Based on the PDQ-39 → questionnaire
- (5) Evaluation of the freezing of gait questionnaire (FOG-Q) → questionnaire
- (6) Evaluation of walking ability: walking distance in 30 seconds, 10m natural walking time and number of steps, Timed Up and Go test, 360° rotation test → conducted in the rehabilitation room
- (7) Video recording of the walking state → conducted by the subject in the rehabilitation room.

### 13. Evaluation items

#### 13.1. Efficacy endpoints

##### 13.1.1. Primary endpoint (primary endpoint)

<PART1>

Comparison of 30-second walking distance between SMA and sham stimulation

<PART2>

Comparison of 30-second walking distance between M1 and sham stimulation

[Rationale for setting]

As a basis for setting the primary endpoint, patients with sloping feet may have a decrease in walking speed, but in severe cases, they may not be able to walk at all when walking, and they may not be able to achieve almost any walking distance. Even in such a case, if the walking distance is taken as the

primary endpoint, it can be left as data. On the other hand, the 10-m walking time set as a secondary endpoint may not be available for such severe cases, and the patient may have to be excluded. Therefore, walking distance was set as the primary endpoint.

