| Purpose of the study                                                          |                    | To examine the effect of transcranial direct current electrical stimulation on freezing of gait                                                                                                                                                                                                                                                                                                                                                                                                                                                                                                                                                                                                                                                                                                                                                                                                                                                                                  |
| Phase                                                                         |                    | N/A                                                                                                                                                                                                                                                                                                                                                                                                                                                                                                                                                                                                                                                                                                                                                                                                                                                                                                                                                                              |

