Not applicable

■ A person who supervises research other than the principal investigator and principal investigator

Not applicable

■ Clinical laboratories, medical and technical departments and institutions related to clinical research

Not applicable

■ Contract Development Organizations

Not applicable

2. Background of clinical research

Parkinson's disease (PD) is a progressive intractable neurological disease characterized mainly by motor symptoms such as tremor, rigidity, akinesia, and postural reflex disorders. Although no curative treatment has been established at this time, the pathology is considered to be abnormal function of the basal ganglia, and as symptomatic treatment, replacement therapy of dopaminergic drugs and neuromodulation to modify the functional abnormality of the basal ganglia. Deep brain stimulation (DBS) therapy for the subthalamic nucleus and globus pallidus has been done. As a result, many of the motor symptoms have become controllable, but there are still treatment-resistant motor symptoms, which are an issue for the future. In particular, "freezing of gait" is a condition in which the sole of the foot becomes stuck to the floor at the start of walking or when changing direction, and is one of the most troublesome symptoms of PD. It is a major cause of falls and a factor that significantly reduces the patient's activities of daily living. In particular, when the drug is on, drug therapy and DBS are completely ineffective, and mechanisms other than dopamine may be involved. Treatment is extremely difficult, and the development of new treatments is desired. Although the pathophysiology of slurring feet has not yet been clarified, it is rooted in impaired gait rhythm due to incontrol of stride length and gait, and in recent years functional MRI analysis has pointed out a decrease in neural activity not only in the basal ganglia but also in the cerebral cortex, supplementary motor cortex and frontal lobe.

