Transcranial direct current stimulation (tDCS) is a non-invasive stimulation method in which a weak (0.5 to 2 mA) direct current passes through the skull from an electrode placed on the scalp and modifies cortical excitability directly under the electrode. tDCS can alter brain function to excitatory or inhibitory depending on the polarity of the electrodes placed in the targeted cortical region. That is, under the anode, the cell membrane is depolarized and cortical excitability increases, and under the cathode, hyperpolarization occurs and excitability decreases. Since the effect persists for a certain period of time (from a few minutes to about 1 hour) after the stimulation ends, it has been pointed out that it may also

change the plasticity of synapses. In addition, tDCS is relatively inexpensive for both stimulators and electrodes, and since it is compact, lightweight, and easy to transport, it is possible to stimulate the patient while actually walking. Since tDCS to the primary motor cortex has been reported to enhance voluntary contractions and improve motor function, clinical application in post-stroke rehabilitation has been promoted in Japan in recent years. In this study, tDCS is used to neuromodulate the cerebral cortex (supplementary motor cortex (SMA) stimulation and primary motor cortex (M1)). We will examine the possibility that stimulation can improve freezing of gait. In this study, we used a commercially available tDCS device (Halo Sport) to improve the motor function of athletes. Since this device is relatively inexpensive, compact and lightweight, and can be stimulated while actually walking, we aim to apply this device to the treatment and rehabilitation of freezing of gait.

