### 3. Objectives of clinical research

We will examine the possibility of that neuromodulation to the supplementary motor cortex (SMA) or primary motor cortex (M1) by transcranial direct current stimulation (tDCS) improves freezing of gait in Parkinson's disease. If a certain effect is obtained from this research, we would like to lead to the development of a new treatment method for freezing of gait, for example, by combining this method with rehabilitation.

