### 6.1. Criterias of choice

- 1) Male and female patients 20 years of age and older (including age and gender)
- 2) Patients who have been diagnosed with Parkinson's disease who are hospitalized at the Department of Neurosurgery or the Department of Neurology, Juntendo University Hospital for examination or treatment
- 3) Patients with symptoms of freezing of gait
- 4) Patients who have received a sufficient explanation for their participation in this study and have obtained written consent of their own free will after sufficient understanding

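### The objective is freezing of gait, but walking distance is not specific to freezing and no primary or secondary endpoint is named as a freezing count or duration, so a gain in speed alone could be read as less freezing

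*Protocol*

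**What the plan says.** The Research Summary gives the purpose as "To examine the effect of transcranial direct current electrical stimulation on freezing of gait", and section 3 asks whether stimulation "improves freezing of gait in Parkinson's disease". Section 2 describes freezing as a state in which "the sole of the foot becomes stuck to the floor at the start of walking or when changing direction".

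The primary endpoints in section 13.1.1 are "Comparison of 30-second walking distance between SMA and sham stimulation" (PART 1) and "Comparison of 30-second walking distance between M1 and sham stimulation" (PART 2). The rationale is that affected patients may walk more slowly, that severe cases may cover almost no distance, and that distance can still be recorded for them when a 10 m time may not be. It concludes: "Therefore, walking distance was set as the primary endpoint".

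Other provisions bear on the point:
- **Secondary endpoints (13.1.2):** 10 m walking time and steps, Timed Up and Go, and the 360-degree test. None is described as a count or duration of freezing.
- **Video (13.1.3, 12.1, 15.3):** exploratory, recorded after sham and after stimulation in both parts. Specialists are to read it, but section 15.3 ties that reading to improvement having been seen.
- **FOG-Q (12.1):** at screening only.
- **Entry (6.1):** "Patients with symptoms of freezing of gait", with no requirement that freezing be seen at testing.
- **Drug state (10.3):** off-state evaluation is specified for patients with large motor fluctuations.

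**The concern.** Distance in 30 seconds combines how fast a patient walks with how long the patient is stuck. The objective concerns the second component, and the endpoint measures their product. If stimulation, knowledge of being stimulated (section 7.3) or a second attempt after sham (section 5.3) makes patients walk faster while they freeze as much as before, distance rises. Nothing in the primary or secondary tier then shows that freezing was unchanged.

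The opposite error is also possible. A patient who reports freezing but does not freeze during the test contributes a paired difference with no freezing component. Such patients pull the mean anti-freezing effect towards zero.

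The video could separate the two. As written, however, it has no named freezing measure, and its review depends on the result being favourable, so freezing would not be assessed evenly across patients and conditions.

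**Working it through.** The protocol gives no effect size, standard deviation, significance level or power. Its target of 20 comes from feasibility (section 15.1), and the point does not depend on it. All speeds, frozen seconds, standard deviations and shares below are assumptions for illustration.

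**1. What distance measures.** Treat the 30 seconds as walking time plus frozen time:

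distance = speed × (30 s − seconds frozen)

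Assume a patient walks at 0.75 m/s and is frozen for 10 s.
- Start: 0.75 × 20 = 15.0 m
- Speed up 10%, freezing unchanged: 0.825 × 20 = 16.5 m
- Freezing cut from 10 s to 8 s, speed unchanged: 0.75 × 22 = 16.5 m

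The two changes give the same endpoint value.

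**2. A patient with no freezing in either condition.** A proportional speed gain g adds speed × 30 × g metres. At the same speed, removing 30 × g seconds of freezing would add as much. For g = 5%, 10% and 15% this is 1.5, 3.0 and 4.5 s, whatever the base speed. At an assumed 0.8 m/s the gains are 1.2, 2.4 and 3.6 m.

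**3. Could a speed-only gain reach significance?** Section 15.3 plans a one-sample t-test or Wilcoxon signed rank test on the paired difference. For the t-test, assume two-sided 0.05, no freezing in anyone, base speed 0.8 m/s and a paired-difference SD of 2, 3 or 4 m. Power comes from the noncentral t with noncentrality (gain / SD) × √n. The smaller n of 15 is an assumed number continuing to PART 2, since section 6.3 allows patients to stop after PART 1.

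| n | Speed gain | Gain (m) | SD 2 | SD 3 | SD 4 |
|---|---|---|---|---|---|
| 20 | 5% | 1.2 | 0.721 | 0.397 | 0.247 |
| 20 | 10% | 2.4 | 0.999 | 0.924 | 0.721 |
| 15 | 5% | 1.2 | 0.580 | 0.303 | 0.192 |
| 15 | 10% | 2.4 | 0.991 | 0.821 | 0.580 |

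If such a speed gain occurred, a significant primary result with no change in freezing would be quite possible.

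**4. Dilution.** If a share q of patients does not freeze at testing, and so gains nothing through freezing, the mean anti-freezing effect is (1 − q) of its size among those who do. For q = 0.2 it is 0.8, and for q = 0.5 it is 0.5. The protocol gives no value for q.

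**5. Does another planned measure separate the two?**
- The 10 m time and Timed Up and Go are affected by speed as well as by freezing.
- The 360-degree test involves turning, a trigger named in section 2, but the protocol does not define what is measured in it.
- FOG-Q is not repeated after either condition.
- Video could separate them, but section 13.1.3 names no freezing measure and section 15.3 ties its review to improvement.

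**The case against.** The case for the design is substantial. The rationale in 13.1.1 does link distance to the severity of freezing, and it keeps in the analysis the severe patients whom a timed walk might lose. Section 2 also roots freezing in poor control of stride and gait rhythm, so stride is not wholly separate from the symptom. Timed Up and Go and the 360-degree test include the situations that provoke freezing. Off-state testing makes freezing more likely in patients with large fluctuations. Video is planned, the study is exploratory, and scoring detail could sit in a statistical analysis plan.

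Much of this stands. Distance is sensitive to freezing, and there is good reason to keep it as primary. What remains is that it is not specific. The tiers of endpoint and the condition on video review are set in the protocol itself, in sections 13 and 15.3, so they are not details left for later.

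A reader might infer more than the documents support:
- *That a distance gain would be reported as improved freezing.* There is no success or reporting rule. Section 13.1.1 frames each part as a comparison of distance, and section 3 speaks of examining a possibility. The gain could be read that way, and no more can be said.
- *That the protocol expects M1 stimulation to raise motor function generally here.* Section 2 says only that "tDCS to the primary motor cortex has been reported to enhance voluntary contractions and improve motor function", as background to post-stroke rehabilitation.
- *That a null result would tell nothing.* Dilution by an unknown share weakens a null result but does not empty it.

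**Conclusion.** The point holds as a mismatch between objective and measurement. The trial asks about freezing, its primary endpoint is sensitive but not specific to freezing, and no primary or secondary endpoint is named as a count or duration of freezing. The one source that could fill the gap is exploratory, has no named freezing measure, and is tied to a favourable result.

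The size cannot be fixed from the protocol. The figures show that speed and freezing can produce identical distances, and that a moderate speed-only gain could reach significance with 15 to 20 patients. They do not show that this will happen, because base speed, variability, speed gain and the share not freezing at testing are all assumed. The choice of distance as primary is not itself an error. The correction is worth making because the recordings and the readers are already planned.

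**What to change.** Keep 30-second distance as the primary endpoint, and make these changes:

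1. **Section 13.1.2:** add as a secondary endpoint the number of freezing episodes and the time frozen during the filmed walking tests. Include the 360-degree turn if it is filmed. The protocol speaks only of recording walking, so this must be confirmed.
2. **Section 15.3:** delete the condition that ties specialist review to improvement. Have the specialists already planned score every patient's recordings after sham and after stimulation, with clips in shuffled order and condition hidden. This is feasible because the device is removed before gait evaluation (section 10.3). It blinds the readers only, since patients still know their condition.
3. **Reporting:** give the number of patients who froze under sham and under stimulation. Treat any split of the primary result by observed freezing as descriptive only, because it selects on data collected after the interventions and there are at most 20 patients.
4. **Sections 3 and 13.1.1:** state that a distance gain without fewer or shorter freezes is a change in walking performance, not in freezing.

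The cost is protocol wording and the scoring of at most 4 evaluations × 20 patients = 80 short video sets (section 10.2 gives the four evaluations). The downside is a narrower claim if freezing does not change.

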#### 13.1.2. Secondary endpoint (secondary endpoint)

10m Natural Walking Time and Number of Steps

Timed Up and Go test

360° rotation test

#### 13.1.3. Exploratory endpoints

Objective evaluation by videography of walking status

#### 13.2. Safety endpoints

Occurrence of adverse events and defects

#### 14. Handling in the event of an outbreak of illness

##### 14.1. Diseases, etc.

###### 14.1.1. Definition of Disease, etc.

"Disease" refers to illness, disability, death, or infectious disease suspected to be caused by the conduct of clinical research, as well as abnormalities in laboratory values and various symptoms.

##### 14.2. Predicted diseases, etc.

Study subjects may experience discomfort such as tingling, itching, headache, or burning sensation on the scalp where the irritation is being applied. In addition, there is a possibility of bruises and fractures due to falls during gait evaluation.

##### 14.3. Unpredictable diseases, etc.

Diseases other than those specified in section "14.2. Predicted Diseases".

##### 14.4. Determination of severity

In the event that a medical device malfunctions are found to be caused by a malfunction that may cause the following diseases, etc., the following diseases must be reported to the administrator of the medical institution within 30 days from the date of learning of the defect, and the report must be reported to the Accredited Clinical Research Review Board described in the implementation plan.

(1) death

(2) Diseases that may lead to death

(3) Diseases that require hospitalization at a medical institution or extension of the period of hospitalization for treatment

(4) obstacle

(5) Diseases that may lead to disability

(6) (3) ~ (5) and diseases that are serious according to death or diseases that may lead to death, etc.

(7) Congenital diseases or abnormalities in later generations

##### 14.5. Responding to research subjects in the event of an outbreak of a serious illness

In the event that a disease is recognized, the investigator shall immediately take appropriate measures.

In addition, in preparation for compensation liability in the event of health damage to the research subjects in connection with the implementation of this study, this study will be enrolled in clinical research insurance. In the unlikely event that serious health damage (death, permanent disability grade 1 or 2)

occurs due to participation in this study, compensation benefits can be received from the relevant insurance.

#### 14.6 Reporting of illnesses, etc.

In the event that the investigator learns of the occurrence of a disease during the conduct of this study, the investigator shall promptly report to the administrator of the medical institution and report to the Accredited Clinical Research Review Board.

When the Accredited Clinical Research Review Board expresses an opinion on a report of a disease, the principal investigator shall respect the opinion and take necessary measures.

In addition, the report to the administrator of the implementing medical institution and the Accredited Clinical Research Review Board shall be made within the following period.

- (1) Outbreaks of any of the following diseases, etc., that are suspected to be caused by the conduct of specific clinical research using unapproved or off-label drugs, etc., and cannot be predicted. 7 days
  - (a) Death
  - (b) Diseases that may lead to death, etc.
- (2) Outbreaks of any of the following diseases, etc., that are suspected to be caused by the conduct of specific clinical research using unapproved or off-label drugs (excluding those listed in (1)): 15 days
  - (a) Death
  - (b) Diseases that may lead to death, etc.
- (3) Outbreaks of any of the following diseases, etc., that are suspected to be caused by the conduct of specific clinical research using unapproved or off-label drugs, etc., and cannot be predicted: 15 days
  - (a) Diseases that require hospitalization at a medical institution or extension of the period of hospitalization for treatment
  - (b) obstacle
  - (c) Diseases that may lead to disability
  - (d) Diseases that are as serious as (a) to (c) and death or diseases that may lead to death, etc.
  - (e) Congenital diseases or abnormalities in later generations
- (4) Matters other than (1) ~ (3) above shall be made at the time of periodic reporting (every year from the date of submission of the implementation plan, within two months after the expiration of the relevant period).

#### 14.7. Remedies

##### 14.7.1. Delivery of salvage drugs, methods of treatment

If the study subject complains of discomfort such as itching, headache, or burning, the stimulation should be stopped immediately.

##### 14.7.2. Emergency treatment such as acute exacerbation

Immediately stop stimulation and immediately take appropriate measures.

#### 15. Statistical matters

##### 15.1. Target number of cases and rationale for setting

Target number of cases: 20

Because this study is an exploratory trial, there is not enough information to calculate the target number of patients based on statistical power. Therefore, from the number of patients hospitalized for the disease (about 500 patients) per year at our hospital, we estimate the number of patients who meet the inclusion criteria and who can consent to participate in the study (about 1 case per month), and the number of patients who can be conducted within the study period (2 years and 6 months) is 20 patients.

##### 15.2. Population to be analyzed

In principle, the target population for efficacy analysis of this study is the target population for

Intention-to-treat (ITT) analysis, which covers all cases, but the following subjects are excluded from the study population.

- 1) Those who do not meet the inclusion criteria
- 2) A person who has never taken measurements with a device.

The target population, including subjects who have undergone tDCS stimulation at least once, will be analyzed as the target population for safety analysis.

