#### 5.3. Clinical Research Outline

In the tDCS stimulation used in this study, it is difficult to blind the presence or absence of irritation because the patient feels discomfort in the scalp when the stimulation is actually performed. On the other hand, in order to eliminate the effects of wearing the tDCS device even in a state where no stimulation is performed (sham stimulation), evaluation is performed with sham stimulation and actual stimulation. In general, patients with Parkinson's disease have large motor fluctuations in symptoms due to drug therapy, so the patient's condition may vary depending on the timing of the examination. Therefore, when conducting a stimulation test, it is considered that an appropriate evaluation cannot be performed unless the sham stimulation and the actual stimulus are evaluated as a set.

In this study, we evaluated the efficacy and safety of SMA stimulation for sham stimulation in PART 1 and the efficacy and safety evaluation of M1 stimulation for sham stimulation in PART 2. Two tests will be conducted. In PART 1, participants will first practice various gait assessment without any intervention. Next, the tDCS device is worn on the head for 20 minutes in a resting state (sham stimulation: no actual stimulation), and then the device is removed and gait evaluation is performed. Thereafter, the tDCS device is attached again, SMA stimulation is actually performed at 2 mA for 20 minutes, and then the

device is removed and gait evaluation is performed. This is PART 1. At this point, a decision is made on whether or not to move to PART 2 in consideration of the patient's condition and the feasibility of gait evaluation for each patient. If it is judged that it is possible to migrate, the test of PART 2 will be conducted at an interval of at least 6 hours after the implementation of PART 1. In PART 2, as in PART 1, various gait evaluations are first practiced without any intervention, and then gait evaluation is performed after 20 minutes of sham stimulation with a tDCS device. After that, the tDCS device is attached again, and M1 stimulation is actually performed at 2 mA for 20 minutes, gait evaluation is performed, and PART 2 is completed.

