## 8. Study Discontinuation Criteria

### 8.1. Discontinuation criteria per study subject

Discontinue the study in the following cases: If you discontinue the study, clarify the reason and fill out the registration form.

- 1) When the consent of the research subject (or the agent) is withdrawn
- 2) When undesirable events such as side effects occur
- 3) When the principal investigator and co-investigator deem it appropriate to discontinue the study for any other reason.

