#### 15.3. Aggregation and Analysis Methods

The background of the study subjects is calculated and aggregated by calculating the mean value and standard deviation for continuous variables, and the frequency and proportion for categorical variables. If the continuous variable clearly does not follow a normal distribution, transform the variable appropriately, such as a logarithmic transformation, and summarize it by mean and standard deviation, or use the median and interquartile ranges as descriptive statistics.

The primary endpoint, the difference in walking distance between 30 seconds after tDCS stimulation and sham stimulation, will be assessed using a single-sample t-test or a Wilcoxon signed rank test.

For the difference in secondary endpoints, 10 m natural walking time and number of steps, Timed Up and Go test, and 360° rotation test after tDCS stimulation and sham stimulation. Evaluate with a one-sample t-test or a Wilcoxon signed rank test.

together with

Video recording of the gait state is performed to objectively analyze the change in the gait state from the perspective of a specialist (neurologist, rehabilitation doctor) when improvement is obtained.

For safety, frequency and proportion (for all subjects) for each adverse event will be evaluated.

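### The safety population in section 15.2 is tied to real tDCS and does not agree with section 15.3, so PART 1 events before stimulation that end participation can drop out of the safety analysis

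*Protocol*

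**What the plan says.** Five parts of the protocol bear on this point.

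- **Safety population (15.2).** The section says that the target population, including "subjects who have undergone tDCS stimulation at least once, will be analyzed as the target population for safety analysis".
- **Safety analysis (15.3).** "For safety, frequency and proportion (for all subjects) for each adverse event will be evaluated". The same section describes the primary endpoint as "the difference in walking distance between 30 seconds after tDCS stimulation and sham stimulation", so it treats tDCS stimulation and sham as two different things.
- **Order of procedures (5.3).** PART 1 opens with practice of the gait tests without any intervention. Then "the tDCS device is worn on the head for 20 minutes in a resting state (sham stimulation: no actual stimulation"), the device is removed and the gait tests are done. Only after that is the device refitted and current given over the SMA. The order is the same for every patient. Section 5.3 also states the aim: "we evaluated the efficacy and safety of SMA stimulation for sham stimulation in PART 1", with the matching aim for M1 in PART 2.
- **Predicted harms (14.2).** Besides scalp discomfort, "there is a possibility of bruises and fractures due to falls during gait evaluation".
- **Stopping a subject (8.1, item 2).** "When undesirable events such as side effects occur".

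**The concern.** Membership of the safety set appears to depend on something that happens only after the patient has come through practice, sham wearing and a gait evaluation. The gait tests themselves carry a predicted risk of falls, with or without current. A patient who falls after SMA stimulation is in the set. A patient who falls in the same test before SMA stimulation, and is stopped for it, may not be.

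Safety against sham is an aim in 5.3. A set selected on having reached SMA stimulation cannot represent the PART 1 sham phase fairly: events that end participation can be counted after current but not before it. The resulting error makes stimulation look worse relative to sham and understates the harm of the trial's own gait testing. Splitting the table by condition would not repair it, because the patients concerned are no longer in the set.

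If 15.3 is instead meant to override 15.2, the protocol gives two populations for one analysis, and the analyst has to choose between them.

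**Working it through.** The protocol states no adverse event rate, so there is no figure of its own to reproduce. The check has two parts: reading the sections against each other, then an illustration.

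**1. Who is in the set under each reading**

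| Patient | 15.2, real tDCS required | 15.3, all subjects |
|---|---|---|
| Event in PART 1 practice or sham phase, stopped before SMA | out | in |
| Event in PART 1 practice or sham phase, goes on to SMA | in | in |
| Event after SMA stimulation | in | in |
| Event in PART 2 sham phase | in (already had SMA) | in |
| Event after M1 stimulation | in | in |

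The readings differ only in the first row, and only in one direction.

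**2. Size**

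Inputs: N = 20 (15.1). q is the chance per patient of a PART 1 pre-stimulation event that ends participation. The protocol does not give q; 2% to 10% is assumed here.

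- Expected events left out = N × q.
- Chance that at least one is left out = 1 − (1 − q)^20.

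| q (assumed) | Expected events left out | Expected patients remaining | Chance of losing at least one |
|---|---|---|---|
| 2% | 0.4 | 19.6 | 33% |
| 5% | 1.0 | 19.0 | 64% |
| 10% | 2.0 | 18.0 | 88% |

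In counts: one such event is reported as 0/19 instead of 1/20 = 5%, and two as 0/18 instead of 2/20 = 10%.

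**3. When the loss is smaller**

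- *Not every event ends participation.* Take a 5% event risk with half of the events followed by discontinuation before SMA. Of 1 expected event 0.5 is kept, and 20 − 0.5 = 19.5 patients remain, so the reported rate is 0.5/19.5 = 2.6% instead of 5%.
- *Sham phases of both parts pooled.* Take a 5% risk in each sham phase, with every PART 1 event ending participation and all 19 remaining patients entering PART 2. The full count is (1 + 0.95)/(20 + 19) = 5.0%. The restricted count is 0.95/(19 + 19) = 2.5%. The pooled sham rate is halved, not zero.

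**The case against.** The strongest reply is that 15.2 does not say only. The sentence speaks of the target population including subjects with at least one stimulation, and 15.3 then gives proportions over all subjects. On that text the patient who falls in the sham phase stays in and nothing is lost. A reader might infer from 15.2 that the protocol definitely excludes everyone without real current; the full sentence does not support that much. What stands is that an at-least-once condition has no purpose unless it sets a threshold, so the restrictive reading is the natural one. The lenient reading has its own difficulty: the target population then seems to point back to the efficacy set defined just above, which drops anyone who never had a measurement with the device. A patient stopped during practice could still fall outside it.

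A second reply is that 8.1 is not applied mechanically. Section 6.3 has the investigator weigh adverse events after PART 1 before deciding on PART 2, and 10.4 allows intensity to be reduced if stimulation is unpleasant. This is right. It means that only events that actually end participation before SMA are affected.

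Third, a reader might infer that the sham event rate as a whole is driven to zero, or that injuries are concealed. Neither follows. PART 2 sham events are kept. Adverse events are scheduled for collection in PART 1, at the transition decision and in PART 2 (12.1), reasons for discontinuation are recorded (8.1), and illnesses are reported (14.6). The event would be absent from the analysis set, not from the study record.

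Fourth, 15.3 plans descriptive frequencies with no split by condition and no test, and a safety set based on exposure is a common convention. That lowers the stakes, but safety against sham is still named as an aim in 5.3. Nor is this detail left to the statistical analysis plan: the protocol fixes the population itself in 15.2, and 15.4 refers only missing and abnormal data to that plan.

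**Conclusion.** The point holds as an inconsistency with a one-directional consequence. Sections 15.2 and 15.3 do not describe the same population. If 15.2 is applied as it most naturally reads, PART 1 events before stimulation that lead to discontinuation before SMA are left out of the safety analysis.

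The size is one patient and one event per occurrence: 0/19 in place of 1/20 for a single case. How likely that is depends on an event risk that the protocol does not give. The conclusion rests on two assumptions: that tDCS stimulation in 15.2 means real current, as it does in 15.3, and that at least some such events end participation under 8.1. If 15.3 governs, no patient is lost and what remains is a wording conflict to settle. In a 20-patient exploratory trial with descriptive safety reporting this is a moderate point, worth correcting because the correction is so cheap.

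**What to change.** In 15.2, define the safety set as all enrolled subjects who started any study procedure: a practice gait test, sham wearing or real stimulation. State in 15.3 that all subjects means this set.

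Tabulate adverse events by phase (PART 1 practice and sham, SMA, PART 2 practice and sham, M1), using as denominator the number of subjects who started each phase. This also gives the comparison with sham in 5.3 a defined numerator and denominator in each part.

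The cost is one sentence in 15.2 and a matching line in 15.3. Adverse events are already collected from PART 1 onward under 12.1, so no new data are needed. The only downside is a possibly higher reported event count.
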